## Abstract

**Background:**

Malignant pleural effusion (MPE) is the build-up of pleural fluid in the space between the lung and chest wall due to advanced cancer. It is treated initially by large volume drainage (therapeutic aspiration). If the fluid reaccumulates, a definitive procedure is performed. There is wide variation in rate of reaccumulation. Patients with rapid reaccumulation often attend hospital as an emergency. Conversely, patients with slow reaccumulation do not need a definitive procedure and may experience cancelled or unnecessary procedures. This study aims to create and validate a multivariable prediction model to predict how quickly pleural fluid will reaccumulate in patients with MPE following therapeutic aspiration.

**Research question:**

Can we predict how quickly pleural fluid will reaccumulate in patients with MPEs?

**Methods:**

A total of 200 patients with known or suspected MPE attending for therapeutic aspiration will be recruited from 5–10 UK hospitals over 20 months. Patients will be enrolled prior to undergoing aspiration. Following this, they will undergo chest X-ray, which will be repeated one week later (treatment as usual). Rate of reaccumulation will be calculated based on change of size of the effusion seen on X-ray. Data will be collected on common clinical biomarkers
*e.g.*, size of effusion on pre-aspiration chest X-ray, volume of fluid drained. This data will be analysed to create a clinical score.

A further validation cohort of 40 patients will be enrolled in parallel with creation of the score.

**Anticipated impact:**

The ability to predict rate of reaccumulation of MPE will enable patients and clinicians to make better informed treatment decisions. For patients with predicted rapid reaccumulation, a definitive procedure could be offered as first-line treatment, rather than a therapeutic aspiration. This will prevent emergency hospital admissions and decrease number of procedures. By contrast, patients whose effusions will recur slowly may avoid an unnecessary procedure.

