Our pilot data demonstrates that the fluid comes back at a very variable rate. Some patients produce pleural fluid quickly and develop rapid onset, severe breathlessness, which results in an emergency hospital attendance. By contrast, some effusions develop more slowly, and patients may attend for a planned drainage procedure that has to be cancelled due to lack of fluid or have an unnecessary procedure. Currently, there is no way to predict the rate of fluid recurrence for each individual patient.

In summary, MPEs are a common cause of breathlessness in patients with advanced cancer. There is wide variation in the rate of fluid accumulation. Rapid accumulation can result in an emergency hospital admission whereas slow accumulation can lead to unnecessary or cancelled procedures.

**
*Why is this research important in terms of improving the health of patients and improving health care services?*
**

This research is important to improve the care offered to patients with MPEs. As part of the pilot work for this study, we surveyed pleural clinicians involved in deciding when patients undergo a definitive pleural procedure for MPE. Over half (58%) reported that their patients often or sometimes get admitted as an emergency with severe breathlessness caused by recurrent MPE. Over one quarter of cancer patients admitted as an emergency die in hospital
^
7
^. Patients do not want hospital admissions, find them tiring and experience unnecessary delays
^
8,
9
^. The results of this research will enable us to identify patients with rapid pleural fluid accumulation so they can undergo an early definitive pleural procedure and prevent emergency hospital admissions.

 This research will also identify patients whose MPE will reaccumulate slowly or not at all. These patients may currently undergo unnecessary definitive pleural procedures or have their procedure cancelled due to lack of pleural fluid. Our survey data demonstrated that 45% of pleural clinicians often or sometimes cancel a pleural procedure due to lack of fluid. This is inconvenient and distressing for the patient.

 Our research will also help clinicians plan pleural services, by identifying which patients require an urgent procedure and reducing unnecessary and cancelled procedures. Our survey revealed that 94% of pleural clinicians thought a score that enabled them to predict how quickly MPEs would recur would help plan their service.

**
*Review of existing evidence*
**

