The feasibility study identified that only 15 of these 20 patients subsequently underwent therapeutic aspiration. This was because thoracic ultrasound (US) performed following enrolment demonstrated that there was insufficient fluid for a therapeutic aspiration or that the fluid was not amenable to drainage. Therefore, we altered the inclusion criteria to specify that patients must have an effusion demonstrated on thoracic US or computer tomography (CT) scan prior to enrolment. This change to the inclusion criteria will ensure that all enrolled patients will undergo therapeutic aspiration.

We plan to analyse data only on patients with a final diagnosis of an MPE because effusions from other causes usually resolve with treatment of the underlying cause and recurrence is not a problem. However, when patients attend for therapeutic aspiration, the final diagnosis may not be known. Of the 15 patients who underwent therapeutic aspiration in our feasibility study, 12 of them had a final diagnosis of malignancy. For the full study, we plan to recruit 200 patients in Phase 1 to include at least 150 with a final diagnosis of MPE and full primary outcome data.

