### Objectives and outcome measures

The primary objective of this study is
**t**o identify candidate biomarkers associated with the rate of pleural fluid accumulation in patients with MPE and to use these biomarkers to develop and validate a clinical score to predict rate of reaccumulation. These biomarkers will be measured at day 0. This will be compared with the rate of pleural fluid accumulation based on increased size of pleural effusion from CXR immediately post-aspiration to day 7
^
12
^.

*Complete list of candidate biomarkers to be assessed for the primary objective*

The candidate biomarkers include:

Patient biomarkers: i) duration of symptoms; type of malignancy; ii) known malignancy or first presentation; iii) severity of pre-procedure breathlessness (measured on visual analogue scale); iv) previous chemotherapy and/or radiotherapy and/or immunotherapy; v) current chemotherapy and/or radiotherapy and/or immunotherapy; vi) current use of diuretics; emergency (
*via* Accident and Emergency (A&E) or acute medical unit) or urgent presentation (
*via* General Practice (GP) or oncology); vii) performance status (assessed using Eastern Co-operative Group scale); and viii) co-morbidities (chronic renal failure, liver disease, cardiac failure).Effusion biomarkers: i) size of effusion on pre-procedure CXR (measured as percentage opacification of hemithorax - this is a validated measure of effusion size); ii) size of effusion on pre-procedure US (measured from hemidiaphragm to top of effusion); iii) side of effusion; iv) volume of fluid drained during therapeutic aspiration (ml); v) degree of pleural fluid septations (categorised as none, mild, moderate or severe) on US; vi) significant non-expandable lung on post-procedure CXR; and vii) pleural pressures measured by manometry (substudy in 20 patients only in Norwich).Pleural fluid biomarkers: i) total protein; ii) pH; iii) glucose; iv) lactose dehydrogenase (LDH); and v) cytology (categorised as positive
*i.e.*, malignant cells present or negative).Serum biomarkers: i) haemoglobin; ii) white cell count, including neutrophil and leukocyte subsets; iii) C reactive protein; iv) total protein; v) estimated glomerular filtration rate (eGFR); vi) LDH; and vii) N-terminal pro-brain natriuretic peptide (NT-proBNP).

**
*Why were these biomarkers chosen?*
**

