### Follow-up visits

**Day seven:** follow-up visit seven days after the therapeutic aspiration (can be done 5–10 days). This is part of standard clinical care for patients to receive results of pleural fluid testing and decide a management plan. Patients standardly have a CXR at this visit and this will be used to reassess size of effusion. At the point, the 7DVQ will be collected and a CRF completed, particularly to assess whether participants have required further pleural fluid drainage or attended the hospital with breathlessness during the seven-day period. During this period the participant is permitted to have any clinically required intervention.
**Second pleural procedure:** this will be performed if clinically indicated for diagnostic or symptomatic reasons. Indications for symptomatic drainage are as follows: symptomatic benefit from initial pleural fluid drainage; significant breathlessness; and significant pleural effusion (defined as at least 25% of the hemithorax on CXR or estimated volume of pleural fluid of at least 500 ml using US). Participants will undergo a further pleural drainage (
*via* thoracoscopy, chest drain or indwelling pleural catheter insertion according to clinical requirement in their individual care pathway). Patients will undergo CXR and US at this visit prior to intervention.
**Day 30:** follow-up by telephone/review of hospital records to determine further pleural procedures, emergency hospital attendances, other treatment for effusion
*e.g.*, chemotherapy, surgery, diuretics.
**Three months:** follow-up by telephone/review of hospital records to determine further pleural procedures, emergency hospital attendances, other treatment for effusion
*e.g.*, chemotherapy, surgery, diuretics. We will also collect health related QoL data using the EQ-5D 5L questionnaire by telephone.

Research staff will informally assess capacity at each follow-up visit. If the investigator believes that the participant has lost capacity to consent, no further data will be collected, and they will be withdrawn. The study data and samples will be used/retained if the participant had consented for this during the initial consent process.

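### The score is said to support a choice made before aspiration, but its single candidate list includes variables that arise only during or after the aspiration

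*Protocol article*

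**What the plan says.** **Intended use.** Anticipated impact (abstract) says that where rapid reaccumulation is predicted, "a definitive procedure could be offered as first-line treatment, rather than a therapeutic aspiration". Elsewhere the wording is broader. The abstract's Background gives the aim as a model "to predict how quickly pleural fluid will reaccumulate in patients with MPE following therapeutic aspiration". The introduction's account of why the research matters speaks of identifying rapid accumulators "so they can undergo an early definitive pleural procedure and prevent emergency hospital admissions".

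**Candidates.** Objectives and outcome measures gives one list for one score, and says of its items: "These biomarkers will be measured at day 0". The list includes "volume of fluid drained during therapeutic aspiration (ml", "significant non-expandable lung on post-procedure CXR", pleural pressure by manometry (20 patients at one site), and pleural fluid protein, pH, glucose, LDH and cytology.

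**Selection.** The section explaining the choice of biomarkers allows principal component analysis to bring the variables down to eight. Sample size and analysis plan screens candidates on variation and missingness, then applies data reduction if appropriate and a selection method such as backwards elimination.

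**The concern.** Replacing the aspiration with another procedure is a decision taken before the aspiration, so every input to the score must exist by then. Eight listed candidates do not, and nothing in the described analysis keeps them out of the model.

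Two things are at stake. A score that contains such a variable cannot be computed for the use named in the abstract. And its reported R² would describe a prediction made with information the clinician does not have at that moment, so it would not tell the reader how well a pre-aspiration score performs. The protocol foresees a Phase 3 study of the score in use, so this needs to be settled before the score is fixed.

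**Working it through.** **1. The plan's own figures.** These were checked to see whether the point rests on a wrong number. It does not.
- Share without MPE: the feasibility study had 12 malignant diagnoses among 15 aspirated patients. 1 − 12/15 = 20%, as the plan states. The exact 95% interval for 12/15 is 52% to 96%.
- Sample size, with n = 150, P = 8 and R² = 0.5: apparent R² = (0.5 × 141 + 8)/149 = 0.527. The optimism is 0.027 (plan: within 0.05). Shrinkage = 1 + (P − 2)/(n × ln(1 − 0.527)) = 0.947 (plan: 0.95).
- The residual SD margin from the chi-square distribution on 141 df is 13.2% (plan: 13%). The half-width for the mean is t × √(13² × 0.5/150) = 1.48 (plan: 1.5). 150/8 = 18.75 participants per variable, as stated.

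**2. Count of candidates** (Objectives and outcome measures).
- Patient 10, effusion 7, pleural fluid 5, serum 7. Total 10 + 7 + 5 + 7 = 29. The patient group has eight numerals, but two further items (type of malignancy, route of presentation) stand without their own numeral and are counted here.
- Arising during or after aspiration: 3 effusion items (volume, non-expandable lung, pressure) and 5 fluid tests. 3 + 5 = 8, and 8/29 = 28%.
- Without the manometry substudy: 7/28 = 25%.

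**3. Timing of each item, from the protocol's own text.**

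| Item | When it exists | Where stated |
|---|---|---|
| Volume drained | end of aspiration | candidate list |
| Non-expandable lung | post-procedure film; defined as failure to re-expand after aspiration | candidate list; reasons for choosing biomarkers |
| Pleural pressure | during aspiration | Baseline assessments |
| Five fluid tests | on fluid sent after the aspiration is described | Baseline assessments |

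The day 0 timing does not settle the matter, because day 0 covers both sides of the procedure.

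**4. Can the described steps let these items through?**
- Screening looks at spread and missingness. Volume, non-expandable lung and the fluid tests are routine measurements and could pass. Manometry, available in only 20 patients, would probably fail on missingness.
- Effusion size is measured in three ways: film, ultrasound and volume drained. With overlapping measures, backwards elimination may keep volume and drop the two that are available beforehand.
- A principal component is a weighted sum of its inputs. If pre- and post-aspiration variables are reduced together, a retained component needs all of them, even if no single late variable is selected by name.

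**The case against.** The strongest reply is that the abstract says such a procedure could be offered, in one sentence on impact, while the stated aim is prediction after an aspiration. An early definitive procedure, fewer cancelled or unnecessary procedures and better service planning can all be decided after a first drainage, when volume and the post-procedure film are legitimate predictors. This stands in part. The candidate list is sound for those uses, but the reply does not make the pre-aspiration use feasible. It shows two uses that need different predictor sets, while the protocol describes one model and does not fix the moment of prediction.

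Retention is also uncertain. Review of existing evidence reports that volume, fluid LDH and cytology predicted a further procedure in one centre, but adds that these variables were not predictive in other centres. Only volume has a second supporting study there. Retention is therefore possible, and the documents do not show that it is likely.

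A reader might infer four stronger points that the documents do not support:
- **Fluid results come only at day 7.** Follow-up visits says of that visit: "This is part of standard clinical care for patients to receive results of pleural fluid testing and decide a management plan". This dates when patients are told. It gives no laboratory turnaround.
- **MPE status is known only after aspiration.** The feasibility section says: "However, when patients attend for therapeutic aspiration, the final diagnosis may not be known". Known malignancy is an entry route, and the restriction to final MPE is reasoned: other effusions usually resolve with treatment of their cause.
- **Inclusion in analysis contradicts that restriction.** Its reference to participants with available data most naturally concerns completeness of data among those eligible for analysis.
- **The whole study serves the pre-aspiration decision.** It is one of several stated uses.

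Fluid results might also exist from an earlier diagnostic sample in some patients, but the protocol takes them from the study aspiration.

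**Conclusion.** The point holds in a limited form. One stated use of the score requires a prediction before aspiration, while 8 of 29 candidates (7 of 28 without manometry) arise during or after it, and the described selection does not take account of this. Followed as written, the plan can produce a score that cannot be calculated for that use, although it could still be used after a drainage.

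The consequence depends on at least one such variable being retained or entering a component. The effect on R² cannot be sized from the documents. The conclusion assumes that the fluid tests come from the study aspiration, as Baseline assessments describes. It does not depend on any error in the sample size, which reproduces, or on the choice of the MPE-only population. Which clinical use the score should have is not for this review to say, but the impact statement and the candidate list must be reconciled. This is an inexpensive improvement to the design, and it leaves the other stated uses of the score intact.

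**What to change.** State the moment of prediction and pre-specify two nested models before the data are analysed:

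1. A pre-aspiration model using only clinical, serum and pre-procedure film and ultrasound predictors, with tumour type entered as known at attendance. This is the only model that should be cited for the claim that a procedure could replace the aspiration.
2. A post-aspiration model adding volume drained, post-procedure film findings and those fluid results available at the time of use, for planning after drainage.

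Any data reduction should be done within each predictor set, so that no component in the first model depends on later variables. If only one model is wanted, limit the impact statement to decisions made after a first aspiration.

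The cost is one further model on data already being collected, and some wording. The pre-aspiration model may show a lower R², but that figure would describe what is achievable at the moment of that decision. Performance in all aspirated patients with known or suspected malignancy could be reported as an optional sensitivity analysis. At the planned 20%, about 0.20 × 200 = 40 of the Phase 1 recruits would fall outside the main analysis.

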## Introduction

### Background and rationale

Patients with cancer develop malignant pleural effusions (MPEs) when fluid collects between the lung and chest wall (the pleural space). MPEs are common, with more than 30,000 new cases per year in the United Kingdom. They are caused by cancers that have spread to the lining of the pleural space and are common in breast and lung cancer and mesothelioma, a type of cancer caused by exposure to asbestos
^
1
^. MPE may be the first presentation of cancer or develop in a patient with known cancer, but sadly always means the disease is not curable. Patients experience breathlessness, chest discomfort and cough
^
2
^.

The development of a pleural effusion occurs due to the excess production of pleural fluid. The pleural space is lined by a single layer of pleural mesothelial cells (PMCs). These regulate the production of pleural fluid through the control of substances passing in between mesothelial cells (
*via* tight junctions) and through cells
^
3
^. Cancer cells in the pleural space stimulate the production of a pleural effusion
*via* inflammatory pathways and release of vasoactive mediators, such as vascular endothelial growth factor (VEGF)
^
4
^. This increases mesothelial permeability
*via* loosening of tight junctions between PMCs, allowing the passage of proteins and fluid into the pleural space. VEGF levels are raised in MPEs
^
5
^. However, the mechanisms are complex and not yet fully understood.

Treatment of MPE aims to effectively relieve symptoms, prevent emergency hospital admission and reduce the number of procedures and cancelled procedures. Patients usually attend a specialist Pleural Clinic as an outpatient for an initial drainage procedure (therapeutic aspiration). This is an effective, simple and quick way of treating symptoms. However, this does not treat the underlying cause of fluid accumulation. Pleural fluid usually comes back, which results in more breathlessness. When this happens, a definitive procedure (chest drain and pleurodesis or indwelling pleural catheter insertion) is performed
^
6
^.

Our pilot data demonstrates that the fluid comes back at a very variable rate. Some patients produce pleural fluid quickly and develop rapid onset, severe breathlessness, which results in an emergency hospital attendance. By contrast, some effusions develop more slowly, and patients may attend for a planned drainage procedure that has to be cancelled due to lack of fluid or have an unnecessary procedure. Currently, there is no way to predict the rate of fluid recurrence for each individual patient.

In summary, MPEs are a common cause of breathlessness in patients with advanced cancer. There is wide variation in the rate of fluid accumulation. Rapid accumulation can result in an emergency hospital admission whereas slow accumulation can lead to unnecessary or cancelled procedures.

**
*Why is this research important in terms of improving the health of patients and improving health care services?*
**

This research is important to improve the care offered to patients with MPEs. As part of the pilot work for this study, we surveyed pleural clinicians involved in deciding when patients undergo a definitive pleural procedure for MPE. Over half (58%) reported that their patients often or sometimes get admitted as an emergency with severe breathlessness caused by recurrent MPE. Over one quarter of cancer patients admitted as an emergency die in hospital
^
7
^. Patients do not want hospital admissions, find them tiring and experience unnecessary delays
^
8,
9
^. The results of this research will enable us to identify patients with rapid pleural fluid accumulation so they can undergo an early definitive pleural procedure and prevent emergency hospital admissions.

 This research will also identify patients whose MPE will reaccumulate slowly or not at all. These patients may currently undergo unnecessary definitive pleural procedures or have their procedure cancelled due to lack of pleural fluid. Our survey data demonstrated that 45% of pleural clinicians often or sometimes cancel a pleural procedure due to lack of fluid. This is inconvenient and distressing for the patient.

 Our research will also help clinicians plan pleural services, by identifying which patients require an urgent procedure and reducing unnecessary and cancelled procedures. Our survey revealed that 94% of pleural clinicians thought a score that enabled them to predict how quickly MPEs would recur would help plan their service.

**
*Review of existing evidence*
**

There has been little research to date studying predictors of pleural fluid reaccumulation. One previous retrospective cohort study found that the size of effusion on CXR prior to therapeutic aspiration, the volume of pleural fluid drained during therapeutic aspiration, the pleural fluid lactate dehydrogenase (LDH) levels and positive pleural fluid cytology predicted a further pleural drainage procedure being carried out in a single centre with a highly protocol-led pathway
^
10
^. However, these variables were not predictive in other centres. This paper demonstrated wide variation in time to a further drainage procedure, with 30% of patients requiring a further procedure within 15 days whereas 52% had not had another procedure at 90 days. Boshuizen
*et al.*, also found that the volume of pleural fluid drained was predictive of need for a further pleural intervention
^
11
^.

 Despite the lack of evidence for predictors of pleural fluid recurrence, our survey demonstrated that 71% of clinicians try to predict how quickly pleural fluid will recur. However, there was no consistent method for doing this. Clinicians based this judgement on variables such as the speed of onset of symptoms, initial size of the effusion, tumour type and previous recurrence rate (based on review of previous radiology/time between previous drainages).

**
*Data from feasibility study*
**

We successfully recruited 20 patients to a feasibility study at the Norfolk and Norwich Pleural Unit from January to July 2019. We screened 40 patients attending the Pleural Clinic for a therapeutic aspiration of their effusion for eligibility and identified 23 eligible patients. Of these, 20 consented to enrolment. All enrolled patients attended the one-week primary outcome follow-up. The feasibility study included qualitative interviewing of the patients and patients were asked about their experience of the study as part of this interviewing. Our results demonstrated that this study is acceptable to patients and recruitment to target is feasible.

The feasibility study identified that only 15 of these 20 patients subsequently underwent therapeutic aspiration. This was because thoracic ultrasound (US) performed following enrolment demonstrated that there was insufficient fluid for a therapeutic aspiration or that the fluid was not amenable to drainage. Therefore, we altered the inclusion criteria to specify that patients must have an effusion demonstrated on thoracic US or computer tomography (CT) scan prior to enrolment. This change to the inclusion criteria will ensure that all enrolled patients will undergo therapeutic aspiration.

We plan to analyse data only on patients with a final diagnosis of an MPE because effusions from other causes usually resolve with treatment of the underlying cause and recurrence is not a problem. However, when patients attend for therapeutic aspiration, the final diagnosis may not be known. Of the 15 patients who underwent therapeutic aspiration in our feasibility study, 12 of them had a final diagnosis of malignancy. For the full study, we plan to recruit 200 patients in Phase 1 to include at least 150 with a final diagnosis of MPE and full primary outcome data.

